### Patient preference

After the fourth refill procedure, patients will be asked to indicate their preference (refill at home, refill in the hospital, no preference or other) for the location of their refills in the future. Additionally, patients will be presented with a survey to evaluate their preferences across several scenarios to conduct a willingness-to-pay analysis.

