### Endpoints

During the baseline assessment, patients are asked to provide information on their demographic and socio-economic background—including sex, age, marital status, ethnicity, years of education, highest

obtained degree, employment status, income, whether or not they receive home care or have an informal caregiver, and household composition — as well as clinical baseline data, such as the year of pump implantation, medication, indication for having an IDD pump. The general data protection regulation principle of data minimization and proportionality will always be considered.

Further, patients will receive questionnaires related to our primary and secondary outcome measures, as described below. Following this initial assessment, patients will be randomized. The randomization list will be created in R, whereby each patient will receive two refills in the outpatient clinic and two refills at home in a randomized order. After each refill, all baseline outcome measures will be reassessed. In addition, secondary outcomes such as patient satisfaction and preference, telemonitoring quality (applicable only for home refills), and safety will be evaluated during follow-up assessments. Health expenditure data will be collected through phone calls. The researchers will call each patient four weeks after the first refill and four weeks after the second refill. Questions will be asked concerning health-economic aspects. These questions will be based on the following variables: consultations, adverse events, hospitalizations, medication, other health-related costs. For more details concerning these questions, we refer to the health economic telephone interview. To prevent test order effects, the test order of the self-reported measures will be randomized for each individual patient at each assessment. After the fourth refill patients will be asked to complete a Discrete Choice Experiment (DCE). Table 1 (section 15) provides an overview of the outcomes, the timing of assessments, and the designated respondents for each questionnaire.

The self-reported measures will be completed online via REDCap (Research Electronic Data Capture) to enhance study feasibility and ensure data security. For participants who are unable to complete the questionnaires online, or in cases where internet connectivity is limited, paper-based versions of the questionnaires will be available.

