### Randomization

The randomization list will be created in R, each patient will receive two refills in the outpatient clinic and two refills at home in a randomized order. The refill procedures are grouped in pairs (one refill at home and one refill in the outpatient clinic) to counter the effect of time-related confounding effects on the dependent variable. This leads to four possible randomization tracks (Fig. 1, section 15).

A list with patient numbers and the group allocation order that results from this randomization procedure will be stored in a sealed envelope. Randomization will take place in the week after the baseline visit.

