#### Willingness-to-pay (WTP)

In addition to the cost-utility analysis, where QoL and life-years play a prominent role, a DCE will be conducted to estimate the WTP for pump refills at home. This preference elicitation method will help inform future reimbursement policy decisions by capturing the broader value that society places on the intervention (85).

A DCE is based on the idea that people's choices between different options depend on specific characteristics, or attributes, of those options. By systematically varying these attributes across scenarios and asking participants to choose between them, it is possible to estimate how much each attribute influences decision-making. This method will allow reverse engineer choice to quantify the impact of changes in attribute levels on choice. The results will complement the health economic evaluation by providing insight into preferences and perceived value from a societal perspective (86).

A literature review has been conducted to obtain the variables that represent the patient-centered values relevant to DCE (87-97). The following attributes will be used:

- Travel time and waiting time
- Person who performs the refill procedure
- Risk of wound infection
- Additional required amount that you should have to pay (non-reimbursed)

Each attribute is divided into multiple levels (Table 2, section 15). By combining different attributes and their corresponding levels, various scenarios can be created. These attributes will be presented in a choice set consisting of two scenarios (A and B), each representing different combinations of attribute levels (Table 2, section 15). Patients will be asked to choose between the two scenarios presented. During the study, patients will be asked to complete the DCE after the fourth refill. An example of such a choice set is shown in Table 3 (section 15).

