#### Sample size calculation

The sample size calculation (G\*Power version 3.1.9.4) is performed on patient comfort, measured with the general comfort questionnaire, as primary efficacy outcome variable after 4 intrathecal pump refill procedures. True mean comfort responses are based on the study of Zhao et al. (2021) (98), and a common standard deviation is calculated based on three studies which resulted in a value of 16.01049 (98–100). This results in an effect size of  $f=0.3035623$ . To conduct a randomized clinical trial with 2 intrathecal pump refill procedures at home and 2 procedures in the outpatient clinic with estimated true mean comfort responses for the outpatient clinic refill of 78.47 and 88.78 for the refill at home, with a common standard deviation of 16.01049, and 85% power to detect differences in means at a 5% two-sided significance level, a total sample size of 82 patients is needed. This sample size considers a 20% loss to follow-up after 4 refill procedures.

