## Tables and Figures

| What? | Patient comfort *                                                                                                                                                    | QoL *        | Pain Intensity * | Pain interference * | Stress *          | Anxiety * | Self-efficacy * | Burden caregivers * | Patient satisfaction | Tele-monitoring quality** + time | Safety                                                    | Health expenditure *** | Patient preference    |
|-------|----------------------------------------------------------------------------------------------------------------------------------------------------------------------|--------------|------------------|---------------------|-------------------|-----------|-----------------|---------------------|----------------------|----------------------------------|-----------------------------------------------------------|------------------------|-----------------------|
| How?  | GCQ                                                                                                                                                                  | MQOL + EQ-5D | VAS              | PROMIS              | Sarsted t AG & Co | STAI      | GSE             | ZBI                 | Likert-scales        | Likert-scales + time expenditure | Overall safety + environmental safety + sterile procedure | Phone calls            | Multiple choice + DCE |
| When? | At baseline * and after each intrathecal pump refill (** only applicable for refills at home)
***Four weeks after first refill and four weeks after second refill |              |                  |                     |                   |           |                 |                     |                      |                                  |                                                           |                        | After last refill     |
| Who?  | Patient                                                                                                                                                              | Patient      | Patient          | Patient             | Salivary sample   | Patient   | Patient         | Caregiver           | Patient              | Researchers                      | Patient + researchers                                     | Patient                | Patient               |

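### Location preference and the DCE are tied to the fourth refill with no provision for patients who stop earlier, so the preference result will describe completers only

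*Protocol*

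**What the plan says.** Preference for refill location is named among the secondary objectives (Protocol 6.2). Its timing is set in 6.3.2, Patient preference: "After the fourth refill procedure, patients will be asked to indicate their preference". The same paragraph adds the willingness-to-pay survey: "Additionally, patients will be presented with a survey to evaluate their preferences across several scenarios to conduct a willingness-to-pay analysis". Section 6.3 says of the DCE: "After the fourth refill patients will be asked to complete a Discrete Choice Experiment (DCE". Section 10.4.3, Willingness-to-pay, agrees: "patients will be asked to complete the DCE after the fourth refill".

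Two places are looser. In Table 1 (section 15) the preference column, which covers both the multiple-choice item and the DCE, reads "After last refill". Section 6.3 also says that "secondary outcomes such as patient satisfaction and preference, telemonitoring quality (applicable only for home refills), and safety will be evaluated during follow-up assessments", without naming a visit.

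The questionnaire lists given after each home and each hospital refill (9.2) contain neither the preference item nor the DCE. Section 11.2 lets participants withdraw at any time, and no exit assessment is described. Section 7.2 states the pairing: "The refill procedures are grouped in pairs (one refill at home and one refill in the outpatient clinic". Section 11.3 states the expected loss: "This sample size considers a 20% loss to follow-up after 4 refill procedures".

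**The concern.** A patient who stops after the first, second or third refill gives no answer on location preference and makes no DCE choices. Patients know where each refill takes place (7.3), and location is exactly what the question asks about. Dislike of one setting is therefore a plausible reason for stopping, and the missing answers could depend on the quantity being measured.

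The timing of data collection is fixed in the protocol. An analysis plan can say how missing answers are handled, but it cannot recover an answer that was never requested. The results at stake are a named secondary objective and a DCE that section 10.4.3 intends as input to reimbursement policy.

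Part of the loss is avoidable on the protocol's own logic. Because refills are paired, a patient has experienced both settings once the second refill is done. Section 10.4.3 already treats that point as a usable comparison, since the within-trial economic evaluation closes just before the third refill. A patient who leaves after refill 2 or 3 could give an informed preference but is not asked for one.

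**Working it through.** **Inputs.** N = 82 and 20% loss over four refills (Protocol 11.3); preference and DCE after the fourth refill (6.3, 6.3.2, 10.4.3); one home and one clinic refill in each pair (7.2). The preference shares below are assumptions, since the protocol gives none.

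**The plan's own figure.** A repeated-measures ANOVA with a between-group factor (2 groups, 4 measurements, the stated f = 0.3035623, two-sided 5%, 85% power) gives 64 patients if the correlation between measurements is taken as 0.5. That correlation is an assumption; the protocol states none. Then 64 / (1 − 0.20) = 80, within two patients of the stated 82. The check below uses 82 as stated and does not depend on how it was obtained.

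**Who answers.** 82 × (1 − 0.20) = 65.6, so about 66 answer and 82 − 66 = 16 do not.

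**Bounds for all 82.** If c of the 66 completers prefer home, the share among all 82 lies between c/82 (no leaver prefers home) and (c + 16)/82 (every leaver does).

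| Completers preferring home (assumed) | Lower bound | Upper bound |
|---|---|---|
| 40/66 = 61% | 40/82 = 49% | 56/82 = 68% |
| 46/66 = 70% | 46/82 = 56% | 62/82 = 76% |
| 53/66 = 80% | 53/82 = 65% | 69/82 = 84% |
| 59/66 = 89% | 59/82 = 72% | 75/82 = 91% |

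The width is 16/82 = 19.5 percentage points in every row.

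**Between the bounds.** Take a completer share of 80% and 20% loss. If no leaver prefers home, the all-patient share is 0.8 × 0.80 = 64%, so the completer figure is 16 points too high. If half do, it is 0.8 × 0.80 + 0.2 × 0.50 = 74%, a gap of 6 points. If leavers match completers, the gap is 0. If leavers favour home more than completers do, the completer figure is too low.

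**Sensitivity to the loss rate.** Around an 80% completer share, with loss d, the range is 0.8(1 − d) to 0.8(1 − d) + d: 76–81% at 5% loss, 72–82% at 10%, 64–84% at 20% and 56–86% at 30%.

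**What an exit offer could recover.** Only patients who leave after refill 2 or 3 have seen both settings. If r of the 16 answer at exit, the width falls to (16 − r)/82. As an illustration, r = 8 gives 8/82 = 9.8 points. The protocol does not say when losses are expected, so r could be anything from 0 to 16.

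**The case against.** **The timing is a coherent choice.** The strongest defence is that asking once, after two refills in each setting, gives the best-informed answer, and the version history shows that the DCE timing was set deliberately. That stands as a reason to keep the fourth-refill question. It is no reason to ask nothing of patients who stop after a completed pair.

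**Table 1 may already allow an exit answer.** For a patient with four refills its wording means the same as the text. For an early leaver it can be read as the last refill actually received. But 6.3, 6.3.2 and 10.4.3 say the fourth refill, so staff could act on either reading. The conflict is small and should be settled.

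**Related data exist.** Comfort, anxiety, satisfaction and patient-rated safety are listed after every refill in both settings (9.2). They could support imputation or sensitivity analysis, so it would be wrong to infer that no analysis can help. They remain weak substitutes: none is a stated preference, and none supplies DCE trade-offs.

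**Bias is not shown.** A reader might infer that the completer result overstates support for home refills. The documents do not support that. They give no dropout reasons, and reluctance to return to hospital would push the other way. The protocol's own proof-of-concept study reports that all 20 patients were satisfied with home refills. The 20% is a planning allowance for the comfort outcome, not a forecast of missing preferences. Nor does any figure show a shift in willingness-to-pay; for the DCE the point is only that early leavers are absent.

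**Asking everyone after refill 2 has a price.** It is tempting to add the preference item for all patients at that point. In an open-label trial with a self-reported primary outcome, declaring a preference midway could influence the comfort answers at refills 3 and 4. This objection stands, and the routine mid-trial question is not recommended.

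**Conclusion.** The point holds as a cheap improvement to a secondary outcome. As written, the preference result describes completers only. With 20% loss, about 16 of 82 patients are never asked, which leaves bounds about 20 percentage points wide: 56% to 76% for an assumed 70% among completers. The numbers rest on the protocol's N and loss allowance, on assumed completer shares, and on extreme cases for those who leave. They bound the possible error and do not estimate a bias, whose direction and size are unknown.

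A reader might also take 16 as the number that a change would rescue. It is the total loss. Patients who leave before completing a pair, or who decline contact, would still be missed; this includes a patient who starts at home and stops after that single visit.

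The primary analysis of the General Comfort Questionnaire and N = 82 are unaffected.

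**What to change.** 1. In Protocol 6.3, 6.3.2 (Patient preference) and 10.4.3 (Willingness-to-pay), state that the preference item and the DCE are given after the fourth refill or, for a patient who stops earlier having had at least one home and one hospital refill, at the last contact.
2. Change the preference column of Table 1 to the same rule. In 6.3, refer the general sentence on follow-up assessments to it.
3. Report preference for all patients who completed at least one pair, with fourth-refill completers shown separately and the number not asked stated.
4. Do not add a routine preference question after refill 2 for patients who continue.

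The cost is a short text amendment and an early-stop questionnaire link in REDCap. Randomization, refill procedures, the primary endpoint and the sample size do not change. The downside is that early-exit answers may rest on one pair rather than two, which is why the two groups should be shown apart.

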## **Study Design**

### Study Design and patient enrollment

The IMPROVE study is a randomized, controlled, cross-over trial to evaluate if intrathecal pump refills at home (Intervention) are better for patient comfort (Outcome) compared to intrathecal pump refills at the hospital (Control) in patients who receive IDD (Population). We will include at least 82 patients, who will each receive two refills in the outpatient clinic and two refills at home.

The physician will briefly explain the IMPROVE study to eligible patients. If the patient is interested, the researcher will explain the study concept and practical aspects of their potential participation. Additionally, the patients will be screened based on in- and exclusion criteria.

The researcher will explain the study to the patient, what's expected for them and what's in it for them. If the patient is positive about participation, IC and contact information will be provided. IC will be obtained on paper. After receiving a signed IC, the IC will be scanned and stored electronically after which the original paper version will be destroyed.

### Randomization

The randomization list will be created in R, each patient will receive two refills in the outpatient clinic and two refills at home in a randomized order. The refill procedures are grouped in pairs (one refill at home and one refill in the outpatient clinic) to counter the effect of time-related confounding effects on the dependent variable. This leads to four possible randomization tracks (Fig. 1, section 15).

A list with patient numbers and the group allocation order that results from this randomization procedure will be stored in a sealed envelope. Randomization will take place in the week after the baseline visit.

### Blinding

The statistician will be blinded to group allocation. Patients and the researchers performing the refills cannot be blinded to the refill location. To minimize bias, patients will complete the study outcome measures electronically, ensuring that the outcome assessor cannot influence their responses.

### Date Range for collected study data

Data collection will take place from 1/AUG/2025 till 1/OCT/2028.

## **Study Population**

### Population of interest

Adult patients receiving IDD, regardless of the indication (spasticity, non-cancer pain) and intrathecal drugs used (morphine, baclofen, other).

### Inclusion Criteria

- Adult patients, 18 years or older
- Actively receiving IDD
- Stable medication dosage for at least 3 months
- Dutch, French or English speaking

## Exclusion Criteria

- Life expectancy < 6 months
- Patients planned for but not yet received IDD implant
- No residence in Belgium

## Study Assessments and Procedures

### Schedule of Activities

[figure not shown]

**Fig. 1:** Study flowchart. Each patient will receive two refills in the outpatient clinic and two refills at home. Created in <https://BioRender.com>

### Detailed Study Assessments/Interventions

| Experimental intervention: Hospital at Home (HAH) |                                                                                                                                                                                                                                                                                                                                                                                                                                                                                                                                                                                                                                                                                                                                                                                                                                                                                                                                                                                                                                                                                                      |
|---------------------------------------------------|------------------------------------------------------------------------------------------------------------------------------------------------------------------------------------------------------------------------------------------------------------------------------------------------------------------------------------------------------------------------------------------------------------------------------------------------------------------------------------------------------------------------------------------------------------------------------------------------------------------------------------------------------------------------------------------------------------------------------------------------------------------------------------------------------------------------------------------------------------------------------------------------------------------------------------------------------------------------------------------------------------------------------------------------------------------------------------------------------|
| Description                                       | 
The experimental intervention consists of two pump refills for each patient, administered at home. The procedure itself will remain unchanged; however, instead of receiving it at the hospital, the refills will be conducted in the patient's home environment. A researcher will visit each patient at their home; this will be performed under remote control.
 
In the hospital pharmacy of UZ Brussels, the day before the refill procedure, a sealed box will be prepared for every patient. This will be stored at room temperature. The prescription and medication label will be double-checked by the hospital pharmacist and the refill team.
 
Once the researcher arrives at the patient's home, the first step will be to set up the telemonitoring system. Both the researcher at home and the researcher in the hospital will log in to a secure web connection. The researcher at home wears smart glasses, enabling full remote visual and audio monitoring. The researcher at the hospital will have the same view as the researcher at the patient's home. The
 |

|                                         |                                                                                                                                                                                                                                                                                                                                                                                                                                                                                                                                                                                                                                                                                                                                                                                                                                                                                                                                                                                                                                                                                                                                                                                                                                                                                                                                                               |
|-----------------------------------------|---------------------------------------------------------------------------------------------------------------------------------------------------------------------------------------------------------------------------------------------------------------------------------------------------------------------------------------------------------------------------------------------------------------------------------------------------------------------------------------------------------------------------------------------------------------------------------------------------------------------------------------------------------------------------------------------------------------------------------------------------------------------------------------------------------------------------------------------------------------------------------------------------------------------------------------------------------------------------------------------------------------------------------------------------------------------------------------------------------------------------------------------------------------------------------------------------------------------------------------------------------------------------------------------------------------------------------------------------------------|
|                                         | 
home researcher will then verbally confirm the pump settings and cross-check the medication label with the prior pump information. A final check is made when the researcher at the patients' home presents the medication label directly to the researcher in the hospital. After completing all verifications, the sterile refill procedure will be carried out again under remote supervision. The researcher at home will be a predoctoral neurosurgical resident, the researcher at the hospital will be a predoctoral researcher schooled in biomedical sciences.
 
Following the refill, a post-refill evaluation using an ultrasound device (Clarius C3 Scanner, Vancouver, Canada) will be performed to confirm that the pump was correctly refilled and that no subcutaneous drug injection occurred. Once this confirmation is secured, the remote connection will be terminated (Fig. 2, section 15). If the procedure cannot be carried out in a clean and sterile manner at the patient's home (e.g., due to poor hygiene or inadequate general body care), the home refill attempt will be considered unsuccessful. In that case, the procedure will be rescheduled and performed at the outpatient clinic within the same week. After the refill procedure, we suggest the presence of a caregiver during approximately 12 hours.
 |
| Smart glasses and telemonitoring | 
To be able to perform refills at home in a safe way, we will test the feasibility of telemonitoring through smart glasses for this procedure. We aim to set up a communication channel between two people: the researcher performing the procedure at home, and another researcher at the VUB. Other practical details are described in the section just above.
 
The Real Wear Navigator 520 will be used to establish this channel. This piece of technology creates an augmented reality, in which high-yield visual and auditive connection can be established. The RealWear Navigator 520 is GDPR-compliant, both Bluetooth and Wi-Fi can be used to connect the device with an external internet source of user's choice. We will create a secure end-to-end connection through Microsoft Teams. The obtained connection will be a solely live connection, none of the visual nor auditive data will be stored.
                                                                                                                                                                                                                                                                                                                                                                                                                             |
| Assessment                       | 
Saliva samples will be obtained with synthetic salivettes (Sarstedt AG & Co., Nümbrecht, Germany) at three different time points: five minutes before the refill, just after the refill and ten minutes after the refill.
 
Immediately after the termination of the teleconnection, the patient will receive a tablet with a link to the relevant questionnaires in the data collection tool. The test order will be randomized, but all will include: GCQ, MQOL, EQ-5D-5L, VAS, PROMIS, STAI, Likert-scale for patient satisfaction, GSE and questions about safety. Additionally, caregiver burden will be assessed using the ZBI. The quality of telemonitoring, duration of the consultation, and safety will be monitored by the researchers (at home and at the hospital).
 
All the above-mentioned data is study-specific, assessment does not occur during routine practice.
                                                                                                                                                                                                                                                                                                                                                                                                                                                   |
| Intervention team                | 
The intervention team consists of two main people: the researcher in the hospital and the researcher at home. The last one is responsible for the refill intervention. This person will go to the patient's home and perform the procedure.
 
The researcher, who will be at VUB/UZB, is the connection and will remain in close contact with the researcher during the refill at home.
 
This team will be supervised by the PI, [name] and indirectly supervised by the outpatient, treating physician of the patient.
                                                                                                                                                                                                                                                                                                                                                                                                                                                                                                                                                                                                                                                                                                                                                                                                         |

| Control intervention |                                                                                                                                                                                                                                                                                                                                                                                                                                                                                                                                                                                                                                                                      |
|-----------------------------|----------------------------------------------------------------------------------------------------------------------------------------------------------------------------------------------------------------------------------------------------------------------------------------------------------------------------------------------------------------------------------------------------------------------------------------------------------------------------------------------------------------------------------------------------------------------------------------------------------------------------------------------------------------------|
| Description          | 
The control intervention consists of standard care. Five minutes before the refill, a saliva sample will be obtained. These synthetic salivettes will be provided by the researchers in each participating center.
 
The refill procedure will be carried out by the physician, following the standard care protocols currently in place at each participating hospital. During the visit, the pump settings are first read out, after which the sterile refill procedure is performed. The intrathecal pump is then refilled with the medication prescribed for the individual patient, either morphine, baclofen, adjuvantia or a combination of them.
 |
| Assessment           | 
After the consultation, the patients will receive a tablet with the relevant questionnaires in the data collection tool. The test order will be randomized, but all will include: GCQ, MQOL, EQ-5D-5L, VAS, PROMIS, STAI, GSE, Likert-scale for patient satisfaction and questions about safety. Additionally, caregiver burden will be assessed using the ZBI. The duration of the consultation, and safety will be monitored by both the researcher at home and the one at the hospital.
 
All the above-mentioned data is study-specific; assessment does not occur during routine practice.
                                                          |

